##### Physical fitness

3.3.1.2

Physical fitness will be measured by push-up exercise capacity (19). Participants will be asked to perform 1-min pushups, which will be counted continuously until a participant is exhausted and breaks the cadence. The procedure will be remotely supervised via Google Meet or other virtual techniques by one of the research team members.

##### Mental health

3.3.1.3

Depression/Trauma symptoms will also be assessed using the modified Beck Depression Inventory (BDI-PC) (53); Patient Health Questionnaire (PHQ-9) (54); and a modified version of Posttraumatic Stress Disorder Checklist (PCL-5) (55). Based on extensive field experience, shorter versions of each type of screener will be disseminated to reduce “questionnaire-fatigue”. Additionally, all suicide/self-harm items have been omitted from the BDI-PC and PCL-5 to avoid the difficulty of triaging “yes” answers for psychiatric referrals in the context of research, rather than clinical assessments.

### Covariates

3.4

Socio-demographic characteristics (i.e., age, sex, educational level, marital status) as well as behavioral health information will be collected via the online survey. Working conditions & fire department culture/policies will be measured post- app usage by means of “health culture” scores (**Table 1**). These scores rate the extent to which a new firefighter perceives that his/her department and co-workers value and promote healthy behaviors. Because we are unaware of any such previously validated instrument, with the input and oversight from our fire service expert panel, we have modified a set of questions from the Fire service Organizational Culture of Safety (FOCUS) survey with the addition of some questions on health-promoting environments used in other occupational settings (56, 57).

**Table 1 T1:** Data Collection during the Pilot Study Phase of the *Surviving & Thriving* app.

Study Measures	Pre-app usage: <1 year from Fire Academy graduation	Post-app usage: 3-6 months of app engagement
Healthy Lifestyle questionnaire	**X**	**X**
Physical Fitness Measure (i.e., 1-min pushups)	**X**	**X**
Mental Health: Depression/Trauma symptoms (BDI-PC, PHQ-9 and PCL-5)	**X**	**X**
“Health Cultures” scores: ratings of each fire station’s/fire department’s environments (working conditions, culture/policies) as to encouraging/discouraging healthy behaviors)	–	**X**

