### Pilot study phase

3.3

This phase of the study aims to demonstrate that enrolled participants from the new firefighter study population can maintain adherence to the HLS app for at least 3-6 months. We will recruit ~50 new firefighters (a separate cohort from those enrolled in the beta testing) and monitor their app usage. App metrics such as session duration, screen views, and user retention within the app will provide insights into how users interact with the app over time. This cohort of new firefighters for the pilot study phase will also assess the HLS app’s ability to maintain/improve HLS parameters (HLS scores, physical fitness, mental health (trauma/depression) screeners). For the purposes of this pilot study, we will conduct a small single arm trial which aims to obtain preliminary evidence of the efficacy of a novel digital intervention and to collect qualitative feedback from a subgroup of target users. Changes in HLS parameters throughout the pilot testing will be evaluated with repeated measures of health metrics pre-and-post app usage among those participants that engaged in the HLS app for 3-6 months. Namely, participants will receive the same lifestyle and mental health questionnaires and fitness test at the two time points: before using the HLS app and at the subsequent follow-up (i.e. 3-6 months after). Both adherence and efficacy results will be adjusted for the potential influence of new firefighters’ demographic characteristics. Effect modification analysis will include fire crew, station and department cultures/policies (measured by the “Health Culture” score as mentioned below in 3.3.4.).

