In the pilot study phase, Aim 3, adherence to the HLS app will be measured continuously as the total number of engagements with the software by each participant over the 3 to 6-month pilot study. This outcome will be supported by other prespecified app-usage metrics facilitated by the Managed IT Services provider (i.e. app user information; sign-ins, quest completion rate for each level, frequency of habit tracker use, and number of missions initiated). The primary outcome for validating the efficacy of the HLS app among the new firefighters’ will be the changes in the HLS score, comparing the participants’ pre- and post- app-usage scores (10). Using a behavior change measure (i.e. HLS score) as a primary outcome is justified in an intervention of short duration (11). As secondary outcomes, we will evaluate changes in 1-min pushups and mental health parameters. In addition, we will examine whether the health culture in various fire service workplace environments, as measured by the Health Culture score, influences the intervention effect of the app on the primary and secondary outcomes.

Generalized linear models will be utilized to assess the effect of the proposed app intervention comparing pre and post HLS scores, mental health scores, and 1-min push-up capacity upon completion of 3-6 months of app usage. All models will have their assumptions verified, using analysis of the residuals and other diagnostic testing. Generalized linear modeling will be used to model changes over time after taking into consideration the specific variance-covariance structure of repeated measurements or using other statistical methods such as generalized estimating equations models. All models will be adjusted for demographic and working conditions and other potential confounders. Interaction terms will also be incorporated into the models to evaluate any potential effect modification by working conditions, cultures, and policies. Statistical significance for all analyses will be considered as a two-tailed *p*<0.05.

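### Health Culture, the planned effect modifier, is rated only after app use, so an interaction with it cannot be read as effect modification

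*Protocol article*

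**What the plan says.** All points are from the protocol article.

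- **Timing.** Section 3.4 (Covariates): "Working conditions & fire department culture/policies will be measured post- app usage". Table 1 agrees: the Health Culture row has a dash before app use and an X after it. The lifestyle questionnaire, push-up test and mental health screeners have an X in both columns.
- **Nature of the score.** Section 3.4: "These scores rate the extent to which a new firefighter perceives that his/her department and co-workers value and promote healthy behaviors". It is a perception, not an external record of department policy. The authors adapted items from existing surveys: "Because we are unaware of any such previously validated instrument".
- **Use as modifier.** Section 3.3 (Pilot study phase): "Effect modification analysis will include fire crew, station and department cultures/policies". Section 3.6 (Statistical analysis) puts the question as "whether the health culture in various fire service workplace environments, as measured by the Health Culture score, influences the intervention effect of the app". This applies to every efficacy outcome, primary or secondary. The same section then plans the test: "Interaction terms will also be incorporated into the models to evaluate any potential effect modification by working conditions, cultures, and policies". The abstract names the same question.
- **Outcome.** The primary efficacy outcome is "changes in the HLS score, comparing the participants’ pre- and post- app-usage scores". The pilot has a single arm of about 50 people and two time points, before app use and 3-6 months later.
- **Adjustment.** Section 3.6 also says "All models will be adjusted for demographic and working conditions and other potential confounders".

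**The concern.** An effect modifier should be fixed before the intervention can act on it. Here the rating is made after 3-6 months with an app that teaches healthy behaviour and includes team missions, community features and a leaderboard. Three routes can link the rating to the participant's own change without any modification:

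- the app, through its team features, changes how colleagues are perceived;
- someone whose habits or mood improved rates the station more kindly;
- the same tendency to answer favourably colours both the self-reported outcomes and the rating. Section 4 (Discussion) itself expects social desirability bias.

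With no control arm and no baseline rating, the data cannot separate these routes from true modification. The Discussion says the pilot is to support a multi-center controlled trial, so a spurious finding that the app works best in healthy-culture stations could mislead that trial's design. A later analysis plan cannot repair this, because a baseline score that was never collected cannot be recovered. The article gives no reason for omitting it and does not list it as a limitation.

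**Working it through.** The article states no power, effect size, SD or sample-size calculation, so there is no planned figure to reproduce. The check has three steps.

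**1. What the interaction estimates.** Let Y0 and Y1 be the pre and post HLS scores, D = Y1 − Y0, and H the single post-app Health Culture score. In the model Y = a + b·time + c·H + d·(time × H), with two measurements per person, subtracting the pre row from the post row gives D = b + d·H + error. So d is the slope of change on a post-app rating, and testing d = 0 is the same as testing that the correlation of D and H is zero.

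**2. How often that test misleads.** Inputs from the article: n = 50 (section 3.5 expects 50 for Aim 3) and two-sided 0.05 (section 3.6). Assumed, because the article gives no value: the correlation r between D and H arising from the three routes above, with true modification set to zero.

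Approximate rejection rate, with Fisher's z: z = atanh(r) × √(n − 3), where √47 = 6.856; rate = P(Z > 1.96 − z) + P(Z < −1.96 − z).

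| r (assumed) | z | Fisher approximation | Simulation, 20,000 trials |
|---|---|---|---|
| 0 | 0 | 5% | 5.1% |
| 0.1 | 0.1003 × 6.856 = 0.688 | 10.6% | 11.0% |
| 0.2 | 0.2027 × 6.856 = 1.390 | 28.5% | 28.3% |
| 0.3 | 0.3095 × 6.856 = 2.122 | 56.4% | 57.1% |

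If only 40 people supply a score, the simulated rates at r = 0.1, 0.2 and 0.3 are 9.5%, 23.9% and 47.4%. When the score is taken before app use and is unrelated to the baseline outcome, the rate stays between 4.7% and 5.3% in every setting run.

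**3. Does a baseline score cure it?** Not by itself. If baseline culture correlates with baseline HLS, regression to the mean enters. With equal variances and a pre-post correlation ρ, the correlation of D with Y0 is −√((1 − ρ)/2). At an assumed ρ = 0.5 this is −0.5. A culture-baseline correlation of 0.3 then gives a correlation with change of 0.3 × (−0.5) = −0.15, and 0.2 gives −0.10. At n = 50 the simulated rejection rates are about 18% and 11%. With the baseline outcome in the model, they return to about 5% (5.0% in both cases, 20,000 trials each). The remedy therefore needs both parts: a baseline score and the baseline outcome in the model.

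**The case against.** **The percentages are built in.** They are the power of a correlation test at chosen values, and nothing in the article supports 0.1, 0.2 or 0.3. This stands. The figures illustrate sensitivity and do not estimate the error in this trial. The ambiguity itself does not depend on the value chosen.

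**Culture is partly stable, and culture experienced during app use is a fair target.** This stands in part. Department policy will not move much in 3-6 months, and the article does not show that reverse influence occurs. But the instrument measures perception, which can move, and with one post-app reading there is no way to check. The counted, remotely supervised push-up test is also less open to shared questionnaire style, though not to the other two routes.

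**It is a small pilot and modification is not the primary outcome.** True, and this limits the weight of the point. It is still a stated objective in the abstract and in section 3.6.

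**Stronger readings that the article does not support:**

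- *A reader might infer that the missing score turns the primary analysis into a complete-case analysis.* The outcome is itself a pre-to-post change, section 3.3 limits it to those who engaged for 3-6 months, and section 3.5 ties usage monitoring to more than three months of use. People without follow-up already lack the outcome, so the added loss is small.
- *A reader might infer that adjusting all models for this score biases the primary pre-post estimate.* That harm is not shown. In one simulated dataset of 50 complete pairs, the pre-post coefficient stayed at 0.6055, the raw mean change, when the score was added as a main effect, both in a GEE and, with the score centred, in a change model. With an uncentred score the intercept of the change model moved to −0.394, which is a matter of coding.
- *A reader might infer that rating and outcomes are collected in one sitting.* Table 1 gives one post-app column and says no more than that.

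**Conclusion.** The point holds for the effect-modification analysis and only there. The modifier is a perceived rating without prior validation, collected solely after the intervention in a single-arm study. A significant time-by-culture term could come from true modification, from the app or its results shaping the rating, or from common response style, and the planned data cannot tell these apart. Under assumed correlations of 0.1 to 0.3, with no true modification and n = 50, the test is significant in about 11% to 57% of trials against a nominal 5%. The conclusion that the term is uninterpretable needs only that such influence is possible. Its size rests wholly on the assumed correlations. The primary pre-post comparison is not called into question. This is a cheap improvement worth making before data collection, since afterwards it cannot be made.

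**What to change.** 1. In Table 1, add an X for Health Culture in the pre-app column. Administer it in the baseline online survey that already collects the lifestyle data, and record time at the current station.
2. In section 3.6, name the baseline Health Culture score as the effect modifier, and include the baseline value of the outcome in the interaction model to limit regression to the mean.
3. Keep the post-app score as a descriptive outcome, for example to show whether perceived culture changed. Label any interaction with it exploratory.
4. Mention in the limitations that, without a control arm, even a baseline score shows only whether culture predicts change during app use.

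Cost: a few more minutes in the baseline survey. Downside: very new recruits will have limited exposure to their station when they first rate it. The recorded time at the station lets the analysis describe this and check sensitivity to it.

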Career firefighter recruits in the US typically undergo formal training in a designated Fire Academy for 12-20 weeks before becoming new or “probationary” firefighters during their first year of service (26). A recent study demonstrated that fire academy training significantly improved recruits’ body composition, aerobic capacity (1.5-mile run), muscular strength (push-up and pull-up), and muscular endurance (10). However, these fitness and health benefits significantly decreased before these recruits finished their probationary period after academy training. Moreover, firefighters after graduating from the fire academy began to exercise less, eat more poorly, and blood pressure continued to increase despite the health/fitness improvements gained during academy training (7, 24, 27). Nonetheless, a recently implemented HLS intervention in firefighters’ academy training showed improvements in healthy lifestyle behaviors, blood pressure, and mental health (11).

The primary aim of this study is to develop and pilot a user-friendly HLS smartphone application (app) tailored towards new probationary firefighters to consolidate and extend academy/training-derived health benefits into firefighters’ first year in the fire service, and then beyond. The first phase of our research project includes the compiling and designing of educational content for a multicomponent lifestyle intervention addressing physical activity, nutrition, sleep, and resilience, the corresponding app software development, and testing of the minimal viable product (MVP). In the second and third phases of this project, we will test the final HLS app prototype’s user-acceptance and effectiveness. The pilot study will evaluate the app’s ability to engage new firefighters and demonstrate whether adherence to the HLS app-based content is associated with measurable health benefits. New firefighters who can maintain a healthy lifestyle during their initial year in the fire service will be more likely to maintain good health behaviors throughout their careers.

We propose the following three aims for the development, usability testing, and piloting of this novel study intervention tool:

Aim 1- HLS app prototype: Develop a smartphone app for future utilization as a digital HLS intervention directed at new US firefighters. Alpha testing by the study team and pre-beta testing by a fire service expert panel will provide feedback on the MVP to enhance the ‘end-user ready’ *Surviving & Thriving* app.

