### Study population & screening procedures

2.1

App development, Aim 1, included alpha testing by the research team and pre-beta testing by a fire service expert panel, which helped refine the app into a pre-consumer version. The research team was comprised of health professionals with expertise in lifestyle behaviors (i.e. nutritionists, exercise physiologist, mental health practitioner, and occupational health physician-clinicians) as well as a UX (user experience) and UI (user interface) designer. The Fire Service expert panel included professionals with current or past experience in firefighting and health promotion in the US fire service. For Aims 2 and 3, the target study population of new firefighters will be recruited from the graduated classes of the research team’s partner fire academies in Connecticut and Massachusetts (MA). These firefighting academies have previously committed to participate in the usability testing and pilot study phases. Each academy trains two classes of fire recruits annually, respectively. The academy staff will assist in the recruitment of previous fire academy graduates and provide information about the study without being directly involved in any research activities. Additionally, the academies will hold an online session for further explanation of participants’ involvement and the online informed consent process. Subsequently, the informed consent form will be distributed to eligible academy graduates. Those who provide consent will specify their preferred contact information for future communication with the study team by text or email.

All new firefighters ≥18 years old, English speakers, and who have completed the training at our partners’ training sites (i.e., Connecticut Fire Academy and Massachusetts Firefighting Academy in Stow, MA) will be eligible to participate in the study, either for usability testing or piloting of the final prototype. We anticipate all recruits at these partner academies will be eligible to participate in this research study, requiring no further screening process. For Aim 2, we will recruit recently graduated firefighters from Stow, MA. For Aim 3, we will recruit fire academy graduates from Connecticut’s fire academy. Therefore, participants in the usability testing will differ from the cohort of probationary firefighters in the pilot phase.

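### Follow-up may fall anywhere from 3 to 6 months with no named term for elapsed time, so the primary change has no defined time point and the adherence total grows with exposure

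*Protocol article*

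**What the plan says.** Section 3.3 describes a single-arm pilot of about 50 new firefighters, each measured twice: "before using the HLS app and at the subsequent follow-up (i.e. 3-6 months after", where the bracket closes. Table 1 in section 3.4 heads the two columns "Pre-app usage: <1 year from Fire Academy graduation" and "Post-app usage: 3-6 months of app engagement". Eligibility in section 2.1 covers adult English speakers "who have completed the training at our partners’ training sites" and sets no narrower limit on time since graduation. On intake, the same section says "Each academy trains two classes of fire recruits annually, respectively", and the pilot cohort comes from the Connecticut academy only.

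The covariates named in section 3.4 are "Socio-demographic characteristics (i.e., age, sex, educational level, marital status", together with behavioral health information, working conditions and the health culture scores. Section 3.6 specifies paired tests, then generalized linear models or estimating equations comparing pre with post. These are adjusted for demographics, working conditions and further confounders that are not named. The primary efficacy outcome is the change in HLS score. Adherence is the total count of engagements per participant over the 3 to 6 months.

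The Introduction gives the study's premise, that after the academy "these fitness and health benefits significantly decreased before these recruits finished their probationary period after academy training". The limitations in section 4 say that the pilot phase may be too short, but mention neither variable timing nor natural decline.

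**The concern.** A pre-to-post change is interpretable only with a time attached. Here the interval may be 3 months for one participant and 6 for another, and both enter the same mean as one change. The estimate then depends on how the follow-up dates happen to fall. Section 4 says that the pilot will support a multi-center controlled trial, and a change without a time point is a weak planning input.

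Two measures depend on the interval by construction. The adherence count accumulates with exposure. The smoking item of the HLS score (section 3.3.1.1) requires six months without smoking, which is as long as the longest permitted follow-up and twice the shortest.

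The article's own premise is that fitness and health behaviors fall after graduation. The place of the interval on that trajectory may therefore matter too, depending on the trajectory's shape.

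**Working it through.** The article gives no effect size, standard deviation or sample-size calculation, so there is no figure to reproduce. The inputs are the two windows in Table 1 and section 3.3, the adherence definition in section 3.6 and the smoking item in section 3.3.1.1.

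**1. Windows.** Let t0 be months from graduation to baseline and d months from baseline to follow-up. Then 0 ≤ t0 < 12 and 3 ≤ d ≤ 6. Follow-up falls at t0 + d, from 0 + 3 = 3 to just under 12 + 6 = 18 months after graduation. The interval d varies by 6/3 = 2.

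**2. Adherence.** For a constant rate of r engagements per month, the total is r × d: 3r at 3 months and 6r at 6 months. Equal activity gives totals that differ up to two-fold.

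**3. Smoking item.** Someone who quits k > 0 months after baseline has been abstinent for d − k months at follow-up. At d = 3 this is below 3, so the six-month condition cannot be met. At d = 6 it approaches 6 only if quitting is essentially immediate. Someone who quit s months before baseline (0 ≤ s < 6) newly gains the point if s + d ≥ 6. That means s ≥ 3 at a 3-month follow-up, but any s at a 6-month follow-up. The same behavior can therefore score differently according to the follow-up date. This is one of seven items, so at most 1 point on the 0–7 score for the people concerned. The article does not give their number.

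**4. Natural change with zero app effect, linear decline.** With a loss of c per month, the change is −c × d: −3c to −6c. t0 drops out, so the baseline window adds nothing to the paired change.

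**5. Natural change, decelerating decline (assumed).** Suppose an eventual loss A is approached with half-life h. Then change = −A × 2^(−t0/h) × (1 − 2^(−d/h)). The table compares the largest case (t0 = 0, d = 6) with the smallest (t0 near 12, d = 3):

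| h, months | Largest, share of A | Smallest, share of A | Ratio |
|---|---|---|---|
| 2 | 0.875 | 0.010 | about 87 |
| 3 | 0.750 | 0.031 | 24 |
| 6 | 0.500 | 0.073 | 6.8 |
| 12 | 0.293 | 0.080 | 3.7 |

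**6. Effect on the test (assumed).** Take A equal to 1 SD of change, n = 50, no app effect, d uniform on 3–6 months, and a two-sided paired t-test at 0.05 (20,000 simulated trials per setting). Across the four half-lives, the test rejects, nearly always in the direction of decline, in:
- 30% to 91% of trials with baselines at 0–3 months;
- 21% to 32% with baselines spread evenly over 0–12 months;
- 5.5% to 14% with baselines at 9–12 months.

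For scale, the change detectable with 80% power is (1.96 + 0.84)/√50 = 0.40 SD. Steps 5 and 6 show what could happen under the stated assumptions; they are not estimates for this trial.

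**The case against.** The strongest reply is that a reader might infer that timing is excluded from the models, and the article does not say that. Section 3.6 allows for unnamed confounders and for modelling change over time, and a fuller plan may add timing terms. This stands: the absence of a named covariate is not in itself a fault. The article does, however, fix the follow-up window and the raw count, and following those exactly gives a poorer estimate.

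Further objections also limit the point:

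- A reader might infer that the year-wide baseline window by itself distorts the change. Under linear decline it does not (step 4). The article gives no rate or shape, and it reports decline in fitness and behaviors, not in the HLS score itself. With two classes a year at one academy, baselines may also cluster rather than spread.
- One participant's follow-up can come earlier after graduation than another's baseline. This is no defect in itself, because each person is compared with themselves.
- Months since graduation at baseline is as fixed within a person as age or education. It can predict the size of the change, but it has no special status as a confounder of the within-person comparison.
- Nothing in the article says that less engaged participants are assessed later, so confounding of the adherence or health culture analyses by follow-up time is only a possibility.
- No comparison with earlier cohorts at a set time is planned, so none is put at risk.
- This is a small preliminary study, and a natural decline would work against the app. That is so for improvement. For maintenance, late baselines under a decelerating decline would make a null app look better.

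**Conclusion.** The point holds for follow-up timing and for the adherence count. As written, the primary HLS change has no single time point, intervals differ up to two-fold, and engagement totals differ up to two-fold between equally active users. These results follow from the stated windows and definitions; the two-fold adherence figure assumes a constant rate of use. The smoking item is a concrete case in which the score itself depends on the follow-up date.

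The part about baseline timing is conditional. It adds heterogeneity only if the post-academy decline is non-linear, and its size rests on an assumed half-life and total loss.

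A reader might also infer that adjusting for timing would isolate the app effect. It would not: in a single-arm study the change at any defined time still contains the natural trajectory up to that time. The correction should be made, but it improves the definition and precision of the estimate and is no substitute for a control.

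**What to change.** 1. Set one nominal follow-up time, counted from baseline, with a narrow window for the primary assessment of all participants.
2. Record the graduation, baseline and follow-up dates for each participant.
3. Model the change with two centred covariates: change = b0 + b1 × (d − nominal d) + b2 × (t0 − mean t0) + the other covariates, centred likewise. Then b0 is the mean change at the nominal time, and t0 enters as a predictor of change.
4. Express engagements per unit time, or count them over a period common to all participants.
5. State in the limitations that, without a control arm, these steps define the time point of the change but do not separate natural decline from the app effect.

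The cost is less scheduling flexibility for shift workers, collection of the graduation date (not among the items listed in section 3.4), and two model degrees of freedom with about 50 participants.
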